##### Immunogenicity

The primary parameter of immunogenicity will be measurement of DTH responses. Secondary parameters include of assessment of T cell responses by measurement of lymphocyte proliferation, ELISPOT and CTL assays.

###### Delayed type hypersensitivity (DTH) responses

At screening, patients will be assessed for DTH response to positive control antigens (a standard “anergy panel” to include candida, trichopyton and tetanus). Patients with no positive response to the anergy panel are not eligible for trial entry. Responses to one of the anergy panel antigens will be subsequently used as a positive control non-modulated antigen. Each antigen will be placed subcutaneously using a tuberculin syringe to inject a volume of 100 l.

DTH responses during the study will be to the control non-modulated antigen and to various vaccine components, specifically the control immunizing antigen KLH, and to aliquots of killed LNCaP cells and LNCaP-M1 cells, to DC/LNCaP cells and DC/LNCaP-M1 cells, and as negative controls, to DCs which have not been peptide pulsed and to saline. DTH response will be assessed by measuring the region of induration surrounding the injection site of each antigen. Each antigen will be placed according to a stereotyped grid, and induration will be read between 40 and 48 hours after injection.

###### Lymphocyte proliferation assay (LPA)

Lymphocyte proliferative response to specific vaccine component antigens (which include the influenza M1 antigen) and to the control antigen KLH.

Lymphoproliferative responses of subject PBMC or purified CD4+ T cells (MACS columns; Miltenyi Biotech) to antigens and mitogens are measured by incubating 1 x 105 cells per well in 96-well U-bottom plates with serial antigen concentrations of protein, recall antigen (tetanus toxoid, KLH) and in separate plates with serial dilutions of PHA, PWM and ConA. After 3 days of incubation with the mitogens and 6 days with the antigens, cells are pulsed with 1 Ci/well of (3H)-thymidine for 6hr and then harvested using the Tomtec (EG&G Wallac, Gaithersburg, MD) and counted in a 1450 microbeta trilux (EG&G Wallac, Gaithersburg, MD). The data are expressed as an LSI (Lymphocyte stimulation Index = (PBMC cpm + antigen or mitogen)/(PBMC cpm + medium)) to define antigen specificity. Individuals are arbitrarily designated as responders or non-responders if their LSI is greater than or equal to 5.

###### ELISPOT analysis

ELISPOT assays for gamma-interferon production from isolated CD4+ and CD8+ T lymphocytes or peripheral blood monocytes in response to vaccine antigen stimulation (or other relevant antigens as they become available) in an overnight culture system.

Ninety-six well plates (Milititer Millipore, Bedford, MA) are coated overnight at 4oC with 5g/ml anti-IFN- Mab (Mabtech, Stockholm, Sweden). The antibody coated plates are washed 4 times with PBS and blocked with RPMI containing 5% pooled human serum (PHS) for 1h at 37 oC.

T cells are added to plates containing anti-IFN- antibodies, and antigen-presenting APCs are added for 12-24 hours. Alternatively, PBMCs or CD8+ T cells purified by magnetic bead antibody cell sorting (MACS columns; Miltenyi Biotech) can be added to the plates. Antigen-presenting APCs may be DCs pulsed with peptides (e.g. HLA restricted influenza or PSMA1/2 peptides) or may be cross-presenting antigen (e.g. apoptotic EL4 cells stably transfected with influenza matrix antigen). 24-48 hours after co-culture of T cells and antigen-presenting APCs, a second biotinylated anti-IFN- antibody is added, followed by an avidin-peroxidase complex. Development with an HRP substrate enumerates IFN- producing cells as demonstrated by “spots” and reported as spot forming cells (SFC). A positive response is defined as >100 SFC per 1x106 T cells. If ELISPOT responses are negative, we will perform “recall” ELISPOT assays, in which purified T cells are stimulated with antigen-loaded DCs for 7 days and then tested for antigen specificity in ELISPOT assays. Only spots with a fuzzy border and a brown color are counted. Responses are considered positive if a minimum of 10 SFCs are counted after the control has been subtracted.

###### Cytotoxic T-lymphocyte (CTL) responses

CTL response against vaccine component antigens (or other antigens as they become available) presented on HLA-restricted target cells in standard bulk chromium release assays.

Cytolytic assays will measure 51Chromium release from target cells to measure circulating effector or memory CTL activity. Freshly derived circulating CD8+ T cells are assayed for their effector CTL activity by monitoring their ability to lyse 51Cr labeled target cells that have been pulsed with HLA-restricted peptides, or which have been virally transduced to express specific antigens via the endogenous or “classical” MHC I antigen presentation pathway. Expansion of central memory T cell responses are assayed by recalling T cells in vitro with antigen-loaded DCs and then assessing CTL activity on labeled targets. We will employ standard means of assaying for HLA-restricted CTLs in patients that are HLA- using 51Cr loaded T2 cells pulsed with defined peptides as target cells. HLA A*0201 restricted peptides have been defined for the influenza M1 antigen (GILGFVTL, amino acids 58-66, (Gotch et al., 1987)). A positive response is defined as >15% cytotoxicity at an effector:target (E:T) ratio of 20:1. Percent cytotoxicity is determined by using the average values of triplicates from experimental wells (E) compared with average values of spontaneous (S) and total (T) release as follows: % cytotoxicity = ((E - S)/(T - S)) x 100.

Percent specific killing will be reported as a measure of lysis of antigen loaded target cells as compared to antigen negative target cells, defined as the median counts per minute (CPM) of gamma particles produced by 51Cr in the supernatants taken from the respective target cell populations.

#### Interim and Final Analysis

Preliminary safety analysis will be performed after each immunization is given. A final analysis will occur after all visits are completed. Final analysis will include an assessment of the relationship between the total number of dendritic cells administered and PSA levels as well as total number of dendritic cells administered and immunologic responses.

### Monitoring and follow-up.

Patients will be monitored intensively at the Rockefeller University Hospital following each vaccination. Patients will be monitored directly for one hour after each vaccination. Patients may stay longer or may be admitted as necessary or at the discretion of the PI. Antihistamines and epinephrine will be available for treatment, as appropriate, of any allergic reactions. The local injection site and draining lymph nodes will be monitored for inflammation and swelling. Patients receiving placebo will not receive DTH tests (other than saline), so as not to tolerize them to subsequent vaccination.

Possible local reactions that should be recorded include erythema and induration (measured using a flexible ruler and pain/tenderness, or warmth at the injection site). Local or systemic reactions will be noted on the case report forms.

In the event of a local or systemic reaction, patients will be monitored until the reaction has resolved. All grade 3 or more severe reactions will require immediate notification of a study physician. Monitoring will include direct supervision by nursing and physician staff, monitoring of vital signs and physical examination as needed, and other appropriate medical measures as deemed necessary.

During the week after each immunization, the subject will be examined or contacted by phone by the investigator or his designee to obtain local and systemic reaction data and to determine the subject’s clinical status. Instructions to subjects leaving the Rockefeller University GCRC post-vaccination will include directions and telephone numbers to use in the event of any unusual or severe sign or symptoms. Subjects reporting such symptoms should be seen in the Rockefeller University GCRC at the time of maximal symptoms, and will be followed up clinically until resolution of symptoms.

Interim outpatient visits will include history and physical examinations as well as monitoring of clinical laboratory studies, as detailed in the schedule of events. Between outpatient visits, for the first 7 days post immunization, a self-assessment questionnaire will be completed by the patient with instructions to notify the study team by phone if any systemic symptoms or unusual or severe symptoms are experienced.

Longer term follow up will be performed at graded intervals following vaccination (weeks 9, 13, 17 and possibly 29 in Arm 1, and weeks 17, 21, 25 and possibly 37 in Arm 2).

#### Monitoring Adverse Events

Subjects having adverse events will be monitored with relevant clinical assessments and laboratory tests as determined by the Investigator. All adverse events must be followed to satisfactory resolution or stabilization of the event(s).

Any actions taken and follow-up results must be recorded on the appropriate Case Report Form, as well as in the subject’s source documentation. Follow-up laboratory results should be filed with the subject’s source documentation.

For all adverse events that require the subject to be discontinued from the study, relevant clinical assessments and laboratory tests will be repeated on at least a weekly basis, until final resolution or stabilization of the event(s).

##### Adverse Events Data Collection

At each study visit, the investigator or designee will collect all information on changes in signs and/or symptoms from baseline, in the form of a targeted history and physical. Laboratory tests will also be obtained to assess safety as described in “Schedule of Events,” and will be reviewed as results become available. For protocol related problems, patients will either be provided with or referred for any medical follow up as necessary. Patients will be referred to their primary care provider for non-protocol related health problems. This information along with the outcome will be recorded as part of the medical record.

The GCRC nursing staff will also assess each patient during inpatient hospitalization. Prior to the start of the study, the GCRC nursing staff will be given a thorough inservice on the study, so that they are well aware of the expected adverse events. Independently of the study team, these nurses will assess for and record any signs or symptoms deviating from baseline in the medical record. They will also report such occurrences directly to the investigator or designee.

##### Adverse Event Reporting

As described above, adverse events data is collected and documented by both the investigator/designee and the GCRC nursing staff. The study nurse practitioner will keep a log of all such adverse events recorded in the medial record, with a start and stop date. Each adverse event will be graded using NCI’s Common Toxicity Criteria, version 3.0, and the relationship of the adverse event to the study treatment will be described per NCI’s guidelines as definite, probable, possible, unlikely, or unrelated. Any medical follow up and outcome of the adverse event is also logged. All expected adverse events are listed in the Post Injection Assessment Form (attached). Any adverse event that is not listed in this form will be considered to be an unexpected adverse event. The nurse practitioner will log each adverse event as either expected or unexpected.

During all inpatient visits, the GCRC nursing staff reports all adverse events using a secure electronic reporting system maintained by the Systems Administrator ([name]) of The Rockefeller University Hospital. This report, generated during the work shift in which the adverse event occurred or was reported, describes the adverse event, any interventions given, and the outcome when known. This report is electronically sent to the Medical Director, the Principle Investigator (PI), the GCRC Clinical Research Officer, the Hospitalist, and the GCRC Pharmacist. The Hospitalist determines each adverse event to be serious or not serious. These reports are then signed and dated by the Hospitalist and retained in the Office of Clinical Research. This process of reporting and reviewing adverse events is independent of the investigator reporting and reviewing.

All adverse events will be tabulated from the AE log and reported to the IRB and FDA in the annual progress report. Information to be reported includes all adverse events, the CTC grade assigned, and attribution to the investigational agent. Total enrollment, demographics of enrollment, protocol violations, current status of subjects (completed, ongoing, dropout), reasons for attrition, the number of subjects reaching primary endpoints, and any available research data will also be reported.

#### Serious Adverse Events

All serious adverse events (defined below), whether or not deemed drug-related or expected, must be reported by the Principal Investigator or designee to the IRB within 24 hours (one working day) by telephone, and to the GCRC Clinical Research Officer. Written reports must follow as soon as possible, which include full descriptions of the event and any sequelae. The PI will report any unexpected and serious adverse event within 7 calendar days by phone or fax to the FDA, and follow within 15 calendar days by written form to the FDA. Any actions taken by the FDA or IRB will be reported by the PI to the NCI.

These stipulations includes serious adverse events that occur any time after the inclusion of the subject in the study (defined as the time when the informed consent is signed), up to 30 days after the subject completes or is discontinued from the study. The subject is considered completed after the completion of the last visit, either as documented in the Study Flow Chart of the protocol. Discontinuation is the date a subject and/or Investigator determines that the subject can no longer comply with the requirements for any further study visits or evaluations (eg the subject is prematurely discontinued from the study; see Stopping rules).

A serious adverse event in this study is defined as any event that:

Is fatal,

Is life-threatening (defined as the patient being at immediate risk of death from the AE as it occurred),

Is significantly or permanently disabling,

Requires in-patient hospitalization, or prolongs hospitalization.

Important medical events that may not fit these criteria may also be considered a serious adverse drug experience when, based upon appropriate medical judgment, they may jeopardize the patient and may require medical or surgical intervention to prevent one of the outcomes listed in this definition.

In addition to reporting serious and unexpected adverse events to the FDA, the PI will also submit in a written report any finding from tests in laboratory animals that suggests a significant risk for human subjects including reports of mutagenicity, teratogenecity, or carcinogenicity within 15 calendar days of the PI’s initial receipt of the information.

Any severe adverse reactions (CTC Grade 3) will also be reported by the PI to the GCRC Clinical Research Officer within 48 hours. Medical intervention will be initiated as appropriate and referred for further care if necessary. The PI will not authorize further administration of the vaccine to other patients until consultation with the GCRC Clinical Research Officer and Rockefeller University’s IRB.

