### Stopping rules

#### Criteria for Subject Study Discontinuation

- Development of an exclusionary condition as outlined in section (6)i.e.2, prior to or during vaccination, with the following exceptions:
  - a course of palliative radiation treatment during the study
- platelet counts that drop > 50% from baseline.
  - hemoglobin that drops sufficiently to require transfusion.
  - if the patient develops an infection requiring treatment as an inpatient.
- Failure by the subject to attend three consecutive clinical study visits.
- Request by the subject to withdraw.
- Clinical reasons judged by the study physician to be life threatening, even if not addressed in the toxicity management of the protocol.
- Completion of week 17 or in some patients, week 29 in Arm 1.
- Completion of week 25 or in some patients week 37 in Arm 2.
- Any dose limiting toxicity. A dose limiting toxicity is defined as:
  1. any grade 2 or greater allergic toxicity or asymptomatic bronchospasm or generalized urticiaria
  2. any grade 3 or greater toxicity (hematologic or non-hematologic)
  3. any grade 2 or greater autoimmune reactions

If a subject discontinues prior to completion of the study, the reason for and date of the discontinuation will be recorded. The date of the last dose of study vaccine will also be recorded. Subjects who discontinue prior to study completion may be replaced at the discretion of the Investigator.

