Severe (Grade 3) or potentially life threatening (Grade 4) local reactions, the Rockefeller University GCRC Clinical Research Officer ([name]) must be notified within 48 hours. For grade 4 local reactions, definitive medical and/or surgical intervention should be undertaken as appropriate. Following Grade 3 or Grade 4 local reaction, further vaccines should not be given to other patients prior to consultation with the Rockefeller University GCRC Clinical Research Officer ([name]), and by the PI in conjunction with the Rockefeller Universities Institutional Review Board (IRB).

Systemic reactions

Systemic reactions will be graded according to the CTC version 3.0 (http://ctep.info.nih.gov).

All nonlocal Grade 3 or 4 reactions (for example, elevated temperature following immunization) thought definitely, possibly or probably related to vaccination, will be reported within 48 hours to the Rockefeller University GCRC Clinical Research Officer ([name]). Further vaccines should not be given to other patients prior to consultation with the Rockefeller University GCRC Clinical Research Officer ([name]), and by the PI in conjunction with the Rockefeller Universities Institutional Review Board (IRB).

The study will be stopped if 1 of 3, 2 of 6, 3 of 9, or 4 of 12 subjects experience dose limiting toxicity as defined under 6.i.m. Stopping rules, 1) Criteria for Subject Study Discontinuation. This applies to subjects in both Arm 1 and 2 while he is receiving the investigational product.

If a patient is injected with a DC-vaccine prior to knowing that a contaminant was present (e.g. prior to a 14-day culture becoming positive), the patient will be immediately contacted and undergo a complete history and physical examination. Blood cultures and appropriate laboratory tests will be drawn.

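### Grade 2 allergic and autoimmune dose-limiting toxicities sit below the 48-hour reporting threshold, so an isolated outpatient or delayed one has no prompt required route to the Clinical Research Officer or the IRB

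*Combined protocol and SAP*

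**What the plan says.** All places are in section (6)i of the combined protocol and SAP.

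- **DLT definition** (Stopping rules, Criteria for Subject Study Discontinuation). Besides any Grade 3 or greater toxicity, the list includes "any grade 2 or greater allergic toxicity or asymptomatic bronchospasm" and "any grade 2 or greater autoimmune reactions". A DLT takes the man off study.
- **Report and hold, general** (Serious Adverse Events). "Any severe adverse reactions (CTC Grade 3) will also be reported by the PI to the GCRC Clinical Research Officer within 48 hours". The hold follows: "The PI will not authorize further administration of the vaccine to other patients until consultation" with that officer and the IRB.
- **Report and hold, by type of reaction** (Vaccine Toxicity). Grade 3 and 4 local reactions go to the officer within 48 hours, and "Following Grade 3 or Grade 4 local reaction, further vaccines should not be given to other patients prior to consultation". For systemic reactions, the 48-hour report and the hold cover "All nonlocal Grade 3 or 4 reactions (for example, elevated temperature following immunization) thought definitely, possibly or probably related to vaccination".
- **Study stop** (Vaccine Toxicity). "The study will be stopped if 1 of 3, 2 of 6, 3 of 9, or 4 of 12 subjects experience dose limiting toxicity". Its scope is then given: "This applies to subjects in both Arm 1 and 2 while he is receiving the investigational product".

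**The concern.** The plan puts a Grade 2 allergic or autoimmune reaction on the same footing as a Grade 3 toxicity for two purposes: removing the man and counting toward the study stop. It does not do so for telling the people outside the study team who can act for the other men. No reason is given for the difference.

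This matters because the product has had no prior human use (Previous human experience), and Risks associated with immunization calls the autoimmune risk small but not measurable. Autoimmune signals can also come late. Section (9)ii.a describes one person in an earlier dendritic cell study with a transient low-titer ANA at 60 days. A comparable delay after the last vaccine here would fall well outside the one-hour observation and the first week of close contact.

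**Working it through.** The plan states no figure on this point, so there is nothing to reproduce. The check sets the reporting routes side by side and then sizes the gap under stated assumptions.

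**1. Which route catches an isolated, non-serious Grade 2 allergic or autoimmune DLT?**

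| Route (section) | Trigger | Catches it promptly? |
|---|---|---|
| 48-hour report and hold (Serious Adverse Events) | CTC Grade 3 | No |
| 48-hour report and hold (Vaccine Toxicity) | Grade 3-4 local; Grade 3-4 systemic, at least possibly related | No |
| 24-hour IRB notice (Serious Adverse Events) | Serious events; other important medical events at discretion | Only if classed as serious |
| Same-shift nursing report (Adverse Event Reporting) | Any grade, inpatient visits | Reaches the officer if inpatient, not the IRB |
| Immediate notice to a study physician (Monitoring and follow-up) | Grade 3 or more | No |
| Safety analysis after each immunization (Interim and Final Analysis) | Every immunization | No recipient, threshold or action named |
| SAE stopping rule (Biostatistical analysis) | Serious events | No |
| Team review with the officer (Ongoing Data Monitoring) | Monthly | Up to a month later |
| IRB and FDA tabulation (Adverse Event Reporting) | Annual | Up to a year later |

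For an outpatient or delayed event, only the last two rows are firm.

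**2. Does the study stop cover it?** One DLT reaches the limit only at 1 of 3. After that, one event is below 2 of 6, 3 of 9 and 4 of 12. No limit is stated beyond 12 subjects, although all 24 men are due to be vaccinated. The text does not say whether the count is pooled or per arm.

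**3. Delayed events.** Under Duration, Arm 1 is vaccinated to week 7 and followed to week 17. Arm 2 is vaccinated to week 15 and followed to week 25. Each has 17 − 7 = 25 − 15 = 10 weeks of follow-up, longer in selected men. A 60-day delay is 60/7 = 8.6 weeks, inside that period. The scope sentence of the study stop neither clearly includes nor clearly excludes it.

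**4. How often?** The documents give no rate for these events. Let p be an assumed chance per vaccinated man, independent between men. The chance that at least one event occurs and none falls in the guarded men is:

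- pooled count (3 men guarded): (1−p)³ − (1−p)²⁴
- per-arm count (6 men guarded): (1−p)⁶ − (1−p)²⁴

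| p | Pooled | Per arm | Expected events, 24p |
|---|---|---|---|
| 2% | 0.9412 − 0.6158 = 33% | 0.8858 − 0.6158 = 27% | 0.48 |
| 5% | 0.8574 − 0.2920 = 57% | 0.7351 − 0.2920 = 44% | 1.2 |
| 10% | 0.7290 − 0.0798 = 65% | 0.5314 − 0.0798 = 45% | 2.4 |
| 20% | 0.5120 − 0.0047 = 51% | 0.2621 − 0.0047 = 26% | 4.8 |

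At each assumed rate these percentages are upper bounds on the gap. They still include serious events and inpatient events, which are already reported promptly.

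**5. What happens before the monthly review?** Planned accrual is 16 men in 12 months (Overall Plan for following year), taken as uniform and 8 per arm. Expected vaccine visits per man in the first 52 weeks are (51+49+47+45)/52 = 3.69 in Arm 1 and (43+41+39+37)/52 = 3.08 in Arm 2. The total is 8 × 3.69 + 8 × 3.08 = 54.2. For the other 15 men this is 54.2 × (15/16)/12 = 4.2 visits a month, and 15 × 4/12 = 5.0 at steady state. With an average wait of half a month, about 2.1 to 2.5 visits by other men would precede the officer's scheduled view. These are visits, not predicted harms.

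**The case against.** The strongest reply is that the tiers are deliberate. Removing one man at Grade 2 while pausing all other men only at Grade 3 is coherent, because a hold falls on men who had no event. That stands. A reader might infer that every Grade 2 DLT must automatically halt dosing; nothing in the documents requires it. A hold also has a price. If it lasted 7 days (an assumption; no turnaround is stated), 4.2 to 5.0 visits a month × 7/30.44 gives 0.97 to 1.15 visits caught. A quarter of these, 0.24 to 0.29, would be first injections, which are fixed at day 8 or 9 after leukapheresis.

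A second reply is that the event would not go unseen. Grade 2 or higher signs are recorded, each man is contacted or examined in the week after immunization, and he completes a 7-day self-assessment. Events requiring discontinuation are followed at least weekly, and an important medical event may be classed as serious. This also stands, and it rules out the reading that such events would be missed. But these routes inform the study team or depend on its discretion. None requires prompt notice to the officer or the IRB.

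A third reply is that the supporting evidence is thin. The 60-day ANA was a single finding, without clinical autoimmunity, after a different product. The lung vasculitis (3 of 3 mice against 0 of 3 controls) and the rise in strongly reactive ANA occurred only in the roughly 300-fold dose group, which was meant to provoke toxicity, and no animal had clinical toxicity. I agree, and the point does not rest on these data. It rests on the plan's own DLT definition.

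**Conclusion.** The mismatch is in the text, and no other section closes it for one kind of event: an isolated, non-serious Grade 2 allergic or autoimmune DLT after the first three treated men (or the first three per arm) that is outpatient or delayed. For that event the required notice is monthly to the officer and annual to the IRB, although the man is taken off study.

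The size is modest and uncertain. At assumed rates of 2% to 20%, the 26% to 65% is illustrative and should not be read as the probability of the gap itself. A reader might also infer that delayed DLTs are excluded from the study stop; the wording only leaves this unclear. The point is a cheap safety improvement for a first-in-human immune product. It is not evidence that the tiered holds are wrong.

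**What to change.** 1. Under Serious Adverse Events and Vaccine Toxicity, require the 48-hour report to the Clinical Research Officer for any Grade 2 or greater allergic or autoimmune DLT that is at least possibly related, whether found during dosing or follow-up. The officer and the IRB then decide whether to hold dosing of other patients. An automatic hold for every Grade 2 DLT is optional.
2. Under Serious Adverse Events, replace CTC Grade 3 with Grade 3 or higher, to match Outcome Parameters, Monitoring and follow-up, and the DLT definition. Grade 4 and fatal events are largely covered elsewhere already, so this is mainly for consistency.
3. When making these edits, say in one sentence whether a DLT found in follow-up counts toward the study stop.

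The cost is wording in two sections, with no new visits, tests or patients. At the assumed rates it adds at most about 0.5 to 5 reports across 24 men (24p = 0.48 to 4.8). The new trigger should name the allergic and autoimmune items, not every DLT. The Grade 3 item in the DLT list has no attribution test, so tying the trigger to it would bring in unrelated events in men with progressive cancer.
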